#### Safety

Study procedures and parameters are in accord with safety and application guidelines for tDCS [52]. Treatment will be delivered by personnel trained in tDCS administration. A case record form for each trial participant will be kept to monitor session attendance and any side effects or adverse events according to prespecified criteria. Any protocol violations will also be recorded there. To ensure safety, participants’ blood pressure and pulse will be monitored before and after each stimulation. TDCS is generally well-tolerated and is associated with relatively minor side effects. According to the review of 567 tDCS sessions, adverse events (and occurrence rates) included: tingling sensation (70.6%); moderate fatigue (35.3%); light itching sensation under the stimulation electrodes (30.4%); headache (11.8%); nausea (2.9%); and insomnia (0.98%) [53]. Another review of 209 tDCS studies found similar rates of adverse events in both real and sham stimulation groups [54]. In the event of mild side effects (e.g. a slight headache) participants will not be withdrawn but will be able to discontinue tDCS treatment if they wish. TDCS will be immediately halted if the participant experiences a more serious adverse event or if any other indicators of serious medical risk emerge. Treatment will only be restarted if it is deemed safe to continue by a medical professional. Standard King’s College London insurance and NHS indemnity arrangements will apply to this study.

### Procedure

A flowchart outlining study procedures is presented in Fig. 1. Table 1 presents the time schedule of enrolment, interventions and assessments, consistent with the figure provided in the SPIRIT Statement (2013) [55] recommendations for reporting protocols (see Additional file 1 for SPIRIT checklist).

#### Screening

Potential participants will be referred by their clinician or will self-refer. Researchers will screen participants for eligibility. Screening questionnaires include a tDCS safety screen and a short inclusion/exclusion study specific screen, including an assessment of medical and psychiatric history, and medication dosage and stability. In line with the CONSORT guidelines [56, 57], we will record the number and reasons for any participants we must exclude or any who decline consent or withdraw from the study.

#### Baseline assessment

Once eligibility has been confirmed, the participant’s written informed consent will be obtained by the researcher. Participants will be asked to complete a number of questionnaires and experimental procedures assessing eating behaviours and mood, as well as computer tasks that assess attention bias towards food cues. Once the baseline assessment is complete, participants will be randomly allocated to the treatment ABM + real tDCS or control ABM + sham tDCS groups.

#### Post-treatment assessment

Post-treatment assessment will take place after the last treatment session and include the same elements as the baseline assessment. Blinding success will be evaluated by asking participants and researchers to guess the treatment allocation.

#### Follow-up

Two weeks after post-treatment assessment, a follow-up session will be conducted. This short session will consist of questions regarding mood, food cravings and eating behaviours. Participants’ weight will be measured.

### Measures

#### Screening measures

A tDCS safety screen will be conducted to check for contraindications to tDCS.

#### Outcome measures

Since this is a feasibility study, a broad range of outcome measures are included to determine which are most sensitive to detecting a treatment effect. This will enable us to determine primary outcome(s) for a future large-scale RCT.

#### Clinical outcomes related to eating behaviours

Questionnaires including Eating Disorder Examination Questionnaire (EDE-Q) [58] and Food Cravings Questionnaire-Trait-Reduced (FCQ-T-r) [59] will be administered at baseline and after treatment. The FCQ-T-r will also be administered at a two-week follow-up.Food tasks including the Food Challenge Task (FCT) [40] examining cue-induced food craving and the Taste Test measuring actual food consumption will be administered at baseline and after treatment. Within each session, visual analogue scales (VASs) regarding current experiences (level of hunger, feeling full, urge to eat, feeling low, level of tension, level of stress, level of anxiety) will be completed before and after the food tasks.Computer tasks including the F-AAT [33] and the SRC [60] measuring approach bias towards high-calorie food items will be administered at baseline and after treatment.Participants' body weight will be measured at baseline, after treatment and at follow-up.

#### Other clinical outcomes

Questionnaires assessing: depression - Depression, Anxiety and Stress Scale (DASS-21) [61], cognitive deficits - Montreal Cognitive Assessment (MoCA) [62], and impulsivity - Barratt Impulsiveness Scale (BIS-11) [63] will be administered at baseline and after treatment. The DASS-21 will also be administered at a two-week follow-up.Symptoms of schizophrenia will be assessed by the Simplified Negative and Positive Symptoms Interview (SNAPSI) [64] and rated using the Positive and Negative Syndrome Scale (PANSS-6) [65] at baseline and after treatment.

#### Intervention-related outcomes

Acceptability of the intervention will be measured as follows: (a) before and after each treatment session by collecting VAS scores on the levels of tension, stress and anxiety; (b) before and after each treatment session by asking about any comments about the treatment; (c) at the end of the study, by asking participants if they would like to take part in a therapeutic trial of tDCS if this was available; and (d) by the number of recruited participants.Treatment tolerability will be measured after each session by a VAS assessing levels of discomfort.

#### Blinding

This will be a double-blind study, where participants and researchers conducting assessments and delivering tDCS are blinded to treatment allocation. Sufficient blinding will be ensured by utilising a parallel design and a built-in neuroConn® DC-STIMULATOR blinding feature. With this, real and sham stimulations are assigned different codes, which the researcher enters into the device to start the stimulation. The real stimulation continues for 20 min, whereas the sham stimulation stops after 30 s, which triggers the same sensations on the skin (to improve blinding). To assess whether allocation concealment has been successful, participants and researchers will be asked to guess the treatment allocation at the end of the tDCS treatment and to indicate how certain they are of this guess. Participants will be debriefed and unblinded to group allocation at the end of the study. At that time, participants in the sham condition will be offered ABM + real tDCS treatment following the protocol as described above.

### Analyses

#### Feasibility

The decision as to whether to progress the study to a future large-scale RCT will be based on a number of criteria. These include the number of patients we are able to recruit, the proportion of patients retained, the proportion of patients completing the real and sham ABM + tDCS intervention, the acceptability and tolerability of the tDCS and the effect sizes of treatment outcomes. At the end of the study, these factors will be used to decide the case for progressing to a substantive RCT.

#### Clinical outcomes

Analyses will use the intention-to-treat principle. Descriptive statistical analyses and graphical methods will be used to determine quality, completeness and variability of the outcome measures. The size of the treatment effect on each outcome measure (questionnaires, tasks) will be the difference in outcome data between those in the two treatment conditions after treatment and at follow-up. Group differences will be estimated using linear mixed effects regression models, controlling for the baseline level of the outcome. The aim of the analysis is to establish a suitably precise effect size for the primary outcome at the post-treatment assessment in a future large-scale RCT.

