### Aims

The aims of the present study are to:
establish the feasibility of conducting a large-scale RCT of ABM + tDCS in people with schizophrenia who take antipsychotic medication: this will involve assessing safety (adverse events), recruitment, willingness to undergo random allocation to five sessions of ABM combined with real or sham tDCS, attendance and retention rates;determine the best instruments for measuring outcomes in a future full trial by examining the quality, completeness and variability in the data;estimate the treatment effect sizes and standard deviations for outcome measures to inform the sample size calculation for a large-scale RCT;explore participants’ views on the acceptability, credibility, tolerability and experience of ABM + tDCS.

Based on neuromodulation studies conducted by our group [40, 41] and others [42–44] in people who experience food cravings, we predict that, compared to ABM + sham tDCS treatment, five sessions of ABM + real tDCS applied to the dlPFC will:
decrease approach bias towards food stimuli;decrease state food craving after cue exposure;decrease trait food craving from baseline to post assessment;be considered by patients as an acceptable and useful treatment for antipsychotic drug-induced weight gain.

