### Sample size

As this is a feasibility study, no a priori sample calculation has been conducted. This study aims to provide effect sizes on which future large-scale studies can be based. Total sample sizes of 24–50 have been recommended for feasibility trials with a primary outcome measured on a continuous scale, mainly because estimates of the standard deviation for normally distributed variables tend to stabilise around this size [46, 47]. We have chosen a total sample size of 30 (which exceeds the lower end recommended for feasibility trials).

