### Randomisation

Generation and implementation of the randomisation sequence will be conducted independently from the trial team by a King’s College researcher using Sealed Envelope, an online randomisation tool [48]. Once the baseline assessment has been conducted and the patient is recruited and has consented to the trial, he/she will be allocated to one of the two intervention arms in a ratio of 1:1. Group allocation will be communicated via phone, email or in a sealed non-transparent envelope to the appropriate member of the research team for each participant.

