Possible challenges relate to recruitment/attrition. People with schizophrenia may be ambivalent about receiving tDCS because they may associate it with electroconvulsive therapy. Additionally, people who experience persecutory delusions may not want to undergo the treatment. As participants will be recruited via clinical teams, the aforementioned beliefs may also apply to the clinicians (i.e. the perceived value and cost of the treatment) and this may affect recruitment. To mitigate this, special care will be taken to explain the practical and technical nature of the tDCS to both service users and clinicians. Previous neuromodulation studies in patients with schizophrenia have showed good recruitment rates and adherence to treatment; however, it is unclear whether this can be replicated in the context of weight management. There may be other challenges, e.g. if the participant believes they are receiving sham, or if the treatment is too uncomfortable or too tiring. It is not clear whether participants will be able to distinguish between the real and sham treatment and what impact this will have on attrition rates. TDCS blinding is generally good, e.g. in an RCT for major depressive disorder, tDCS blinding was comparable to that of sertraline [68]. Sensations felt during treatment may interfere with blinding, tDCS can occasionally result in mild discomfort during administration (i.e. tingling, itching or skin redness). However, based on the review of 209 studies, these side effects occur at a similar rate in both real and sham groups [54].

In summary, combined tDCS and ABM is a promising brain-directed treatment for reducing food cravings and food consumption. This innovative feasibility RCT will assess the acceptability and efficacy of this intervention in people with schizophrenia. It will provide a basis for development of future large-scale RCTs and, if results are positive, will provide support for the implementation of it as a treatment.

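### The analysis aims at a suitably precise effect size, but 15 participants per arm give a 95% confidence interval of about ±0.5 to 0.8 SD, too wide to size the next trial or inform progression

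*Protocol article*

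**What the plan says.** All references are to the protocol article.

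- **Clinical outcomes** (under Analyses) states: "The aim of the analysis is to establish a suitably precise effect size for the primary outcome at the post-treatment assessment", and the sentence goes on to refer to a future large-scale RCT. The same section plans linear mixed models adjusted for the baseline value of each outcome.
- **Sample size** reports that no a priori calculation was made. It cites a recommended total of 24 to 50, mainly because "estimates of the standard deviation for normally distributed variables tend to stabilise around this size", and settles on 30: "We have chosen a total sample size of 30 (which exceeds the lower end recommended for feasibility trials". It also states the purpose: "This study aims to provide effect sizes on which future large-scale studies can be based".
- **Randomisation** fixes equal allocation: "he/she will be allocated to one of the two intervention arms in a ratio of 1:1".
- **Aims** includes to "estimate the treatment effect sizes and standard deviations for outcome measures to inform the sample size calculation for a large-scale RCT".
- **Feasibility** (under Analyses) says progression will rest on recruitment, retention and completion, together with "the acceptability and tolerability of the tDCS and the effect sizes of treatment outcomes".

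None of these sections gives a target interval width, a confidence level or an expected interval, or limits the use of the effect estimate because of its imprecision.

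**The concern.** The reason given for 30 participants and the stated aim of the analysis concern different quantities. A total of 24 to 50 is defended because a standard deviation is tolerably well estimated at that size. The aim, however, is a precise between-group effect, which depends on the standard error of a difference between two means of 15 each.

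Imprecision is normal in a feasibility trial and does no harm if the estimate is only described. Here the estimate has work to do: it informs the size of the next RCT and is one of the inputs to the decision to proceed. A reader told that the effect is suitably precise may rely on it for both. An effect too large by chance would lead to an undersized trial, and one too small would lead to an oversized trial or count against a worthwhile programme.

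**Working it through.** **Inputs from the article.** Total sample 30 (Sample size) with 1:1 allocation (Randomisation), so n = 15 per arm; baseline-adjusted model (Clinical outcomes).

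**Assumptions.** The article gives no confidence level, baseline–outcome correlation r or dropout rate. I use 95% two-sided intervals, r from 0 to 0.8 and dropout from 0 to 30%. The Discussion names attrition as a challenge without a figure.

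**The plan's own figure.** There is no power or precision calculation to reproduce. The chosen 30 does lie inside the cited range of 24 to 50.

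**Step 1: half-width for a standardised difference near zero.**

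Half-width = 1.96 × √(2/n) × √(1 − r²), in units of the outcome SD.

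- Unadjusted, 15 per arm: 1.96 × √(2/15) = 1.96 × 0.365 = 0.716. With the t quantile on 28 df it is 0.748.
- r = 0.5: 0.716 × √0.75 = 0.62.
- r = 0.7: 0.716 × √0.51 = 0.51.

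| Analysed per arm | r = 0 | r = 0.5 | r = 0.7 | r = 0.8 |
|---|---|---|---|---|
| 15 (no dropout) | 0.72 | 0.62 | 0.51 | 0.43 |
| 12 (20% dropout) | 0.80 | 0.69 | 0.57 | 0.48 |
| 10.5 (30% dropout, average) | 0.86 | 0.74 | 0.61 | 0.51 |

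The full range is 0.43 to 0.86; about 0.5 to 0.8 is a fair summary.

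**Step 2: what that means for sizing a trial.** Suppose the observed standardised difference is 0.5. The exact unadjusted interval is −0.23 to 1.22, so it includes an effect in the wrong direction. With adjustment the approximate intervals are −0.12 to 1.12 (r = 0.5) and −0.01 to 1.01 (r = 0.7).

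For an unadjusted comparison at 80% power and two-sided 5%, n per arm ≈ 2 × (1.960 + 0.842)² / d² = 15.7 / d²:

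- d = 0.5: 63 per arm
- d = 0.2 (inside the interval): 393 per arm
- d = 1.22 (upper limit): 11 per arm

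In the most favourable cell of the table (0.43) the interval is about 0.07 to 0.93. Required size varies as 1/d², so its two ends differ by a factor of (0.929/0.071)² ≈ 171. Baseline adjustment in the next trial multiplies both ends by the same 1 − r² and leaves that ratio unchanged.

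**Step 3: contrast with the SD.** With 28 df, the 95% limits are √(28/χ²) at the 97.5% and 2.5% points, which is 0.79 to 1.35 times the estimate. Squared, that is 0.63 to 1.83 times the next trial's size. This is still appreciable uncertainty, but it is bounded and can be allowed for. The cited rationale therefore serves the SD, not the effect.

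**Step 4: what useful precision would take.** For an illustrative half-width of 0.3 SD, n per arm = 2 × (1 − r²) × (1.96/0.3)²: 86 at r = 0, 65 at r = 0.5 and 44 at r = 0.7. Even the top of the cited range (50 in total, 25 per arm) gives 0.55 unadjusted.

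**The case against.** Several points on the other side are sound.

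- **Only one section claims precision.** Clinical outcomes does so. Aims and Sample size speak of estimating or providing effect sizes. A reader might infer that all three promise precision; they do not.
- **The sentence is ambiguous.** Because it ends by referring to a future RCT, it could mean that the precise effect is to be established there. It still stands as the aim of this trial's analysis, so rewording is needed on either reading.
- **The article does not say the observed effect will be the planning value.** A reader might conclude that the next trial will simply be sized on it. Aims names SDs beside effect sizes and says only that they inform the calculation, and the Abstract calls the efficacy evidence preliminary.
- **Progression does not turn on the effect alone.** Effect sizes are one of several inputs, with no threshold. The text does not support the stronger reading that a chance result would by itself stop or advance the programme.
- **The unadjusted 0.72 is not the planned analysis.** Baseline adjustment narrows it, which is why the range is given; attrition takes part of that gain back.
- **No threshold defines suitable precision,** so calling the interval too wide is a judgement. It is a safe one, since it holds in every cell of the table.

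The Discussion's closing remark that the study, "if results are positive, will provide support for the implementation of it as a treatment", might be read as a plan to act on a 30-person result. It directly follows a statement about future large-scale RCTs and is not a planned decision, so it is secondary.

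What remains is the mismatch between the claimed precision and the basis for 30, and the use of the effect estimate for sizing and progression with no stated limit.

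**Conclusion.** The point holds in this limited form and should be fixed. The stated precision is not delivered: the 95% half-width is about 0.5 to 0.8 SD, and 0.43 to 0.86 over the whole range examined. This rests on 15 per arm, a 95% level, and assumed correlations and dropout that the article does not give; the conclusion is the same throughout those ranges.

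It would be tempting to go further and call the sample too small. The article does not support that: 30 is reasonable for the feasibility aims and for estimating an SD. The fault lies in the precision wording and in the uses given to the effect estimate.

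**What to change.** 1. **Clinical outcomes:** replace the aim of a suitably precise effect size. For example: *The analysis will estimate the SD, baseline–outcome correlation and completeness of each outcome, and will report baseline-adjusted group differences with 95% confidence intervals; the expected half-width is about 0.5 to 0.8 SD.*
2. **Aims and Sample size:** state that the future RCT will be sized on a justified important difference, using the pilot SD with allowance for its uncertainty, and not on the observed effect. The difference itself can wait, because Outcome measures leaves the future primary outcome to be chosen from this study.
3. **Feasibility:** remove the effect sizes of treatment outcomes from the progression criteria, or keep them with confidence intervals as descriptive information only.
4. **Discussion (secondary):** soften the closing remark about implementation.

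The cost is wording only: no extra participants, procedures or data, and no change to the sample of 30 or to the model. The stated precision will look less favourable.

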## Discussion

Antipsychotic drug-induced weight gain can affect the physical health of people with schizophrenia. Additionally, it can cause individuals to discontinue medication and hence predispose them to relapse [1]. Interventions to prevent weight gain have limited effectiveness in acutely unwell patients who may find it hard to engage in diet or exercise behaviours [7]. There is a need for treatments to prevent weight gain that are easily accessible and can be utilised in various settings.

Non-invasive brain stimulation methods, e.g. tDCS, can be used to target brain areas such as the dlPFC which are associated with cognitive control (including eating) [24]. These have the potential to reduce antipsychotic drug-induced weight gain, e.g. by decreasing food cravings. TDCS can be combined with ABM training to strengthen its effects on retraining approach bias towards high calorie foods. We have described the protocol for a feasibility trial that will inform future studies and add to the evidence of brain-directed interventions for antipsychotic drug-induced weight gain.

Strengths of the study include use of combined neuromodulation and cognitive training. It has been reported that behaviours and cognitions undertaken during or following the tDCS can impair or abolish the effects of stimulation [66]. Administering two interventions concurrently will remove any cognitive interferences and ensure uniform treatment. The protocol is also designed to measure the possible mechanisms of action, e.g. on approach bias and impulsiveness, as well as on clinical symptoms. The protocol adheres to guidance on the optimal conduct of neuromodulation trials [55, 56, 67].

Possible challenges relate to recruitment/attrition. People with schizophrenia may be ambivalent about receiving tDCS because they may associate it with electroconvulsive therapy. Additionally, people who experience persecutory delusions may not want to undergo the treatment. As participants will be recruited via clinical teams, the aforementioned beliefs may also apply to the clinicians (i.e. the perceived value and cost of the treatment) and this may affect recruitment. To mitigate this, special care will be taken to explain the practical and technical nature of the tDCS to both service users and clinicians. Previous neuromodulation studies in patients with schizophrenia have showed good recruitment rates and adherence to treatment; however, it is unclear whether this can be replicated in the context of weight management. There may be other challenges, e.g. if the participant believes they are receiving sham, or if the treatment is too uncomfortable or too tiring. It is not clear whether participants will be able to distinguish between the real and sham treatment and what impact this will have on attrition rates. TDCS blinding is generally good, e.g. in an RCT for major depressive disorder, tDCS blinding was comparable to that of sertraline [68]. Sensations felt during treatment may interfere with blinding, tDCS can occasionally result in mild discomfort during administration (i.e. tingling, itching or skin redness). However, based on the review of 209 studies, these side effects occur at a similar rate in both real and sham groups [54].

In summary, combined tDCS and ABM is a promising brain-directed treatment for reducing food cravings and food consumption. This innovative feasibility RCT will assess the acceptability and efficacy of this intervention in people with schizophrenia. It will provide a basis for development of future large-scale RCTs and, if results are positive, will provide support for the implementation of it as a treatment.

